#### Follow-up questionnaires after discharge from rehabilitation clinic (4, 8, and 12 months after baseline)

To obtain primary and secondary outcome information, short follow-up questionnaires will be sent from the coordinating center to the study participants by mail in study months 4, 8, and 12. Two reminders will be mailed to non-responders within 8 weeks after the first sending of a questionnaire at the 4- and 12-month follow-up. For the 8-month follow-up questionnaire, which contains the information of the primary study endpoint, a high completeness rate shall be ensured by additional replacing the second contact reminder via mail by a contact attempts via telephone. The study participants will have the opportunity to give the information asked for in this questionnaire on the phone.

#### Adherence assessment of patients and their general practitioners

The questionnaire at 8-month follow-up will ask the study participant to list all drugs he/she currently uses and if the take ≥ 80% of the prescribed dose. The pharmacist in the coordinating center will perform a third medication review with the FORTA list and calculate the total FORTA score for the medication used with sufficient adherence at the 8-month follow-up. If this FORTA score at the 8-month follow-up is worse than the FORTA score of the medication at the rehabilitation clinic discharge visit by more than 2 points, the patient will be regarded as non-adherent. It should be mentioned that this is not only an adherence assessment for the patients but also for the general practitioners and other caring physicians in the outpatient setting that may prescribe new or different drugs compared to the intended medication after the patient got discharged from the rehabilitation clinic.

#### Survival follow-up (up to 10 years)

The personal data will be regularly compared with data from registration offices and health authorities to monitor the participants’ vital status and to determine the cause of death of the deceased.

### Statistical analysis plan

#### Sample size estimation

A GHS/QoL score difference of 5.86 scale points was shown to be the minimally important improvement [14], and the study is designed with a sufficient statistical power of 80% to detect such a difference or greater in changes of the score between the intervention and control group with p < 0.05. The sample size calculation was conducted with Proc Power, SAS 9.4, SAS Institute Inc., Cary, NC, USA using data from the first n = 38 study participants of the MIRANDA (***Mi****t Dabei!****R****eh****a n****ach****Da****rmkrebs*) study, which is another study, currently being conducted by the coordinating center (https://www.drks.de/drks_web/setLocale_EN.do). The MIRANDA study recruits colorectal cancer patients in German rehabilitation clinics. The change in the EORTC-QLQ-C30 GHS/QoL score from baseline to the 9-month follow-up was approximately normally distributed. For the estimation of mean ± standard deviation (SD) GHS/QoL score change in the control group in the OPTIMAL study from baseline to 8-month follow-up, the mean ± SD change of the GHS/QoL score from baseline to 9-month follow-up in the MIRANDA study was taken. In the MIRANDA study, the mean ± SD GHS/QoL score increased from baseline (52.41 ± 19.17) to 9-month follow-up (60.96 ± 18.89) by 8.55 (± 16.15) score points. For the estimation of mean ± SD GHS/QoL score change in the intervention group, the minimal important difference of 5.86 points was added (8.55 + 5.86 = 14.41) and the SD was assumed to change proportionally ((16.15/8.55)*14.41 = 27.22).

With these assumptions and applying a significance level of 0.05 and 80% power, n = 462 patients need to be randomized 1:1 to the intervention and control group (i.e., n = 231 patients are needed in each group) to detect a score change difference of 5.86 or more points using a two-sided, two-sample, t-test for the mean difference. Taking into account a drop-out rate of 10% (drop-out defined as no follow-up questionnaire available and/or no documented visit with a study physician at the end of rehabilitation), n = 514 patients need to be randomized.

#### Statistical methods

Homogeneity of the intervention and control group will be described by comparison of the demographic data and key baseline characteristics. All statistical tests will have a two-sided significance level of 0.05. In addition, 95% confidence intervals will be estimated for all outcomes in the intervention and control groups. All analyses will be done using SAS software version 9.4 or later.

The primary analysis will test the null hypothesis:

##### H_0_

The change in the EORTC-QLQ-C30 GHS/QoL score from baseline to 8-month follow-up is the same in the two groups.

versus the alternative hypothesis:

##### H_1_

The change in the EORTC-QLQ-C30 GHS/QoL score from baseline to 8-month follow-up is different in the two groups.

The primary endpoint EORTC-QLQ-C30 GHS/QoL score will be analyzed with an intention-to-treat approach, including all randomized patients in the “Full Analysis Set” who had a documented visit at the end of rehabilitation and have any follow-up data (4-, 8- or 12-month follow-up). If data for the primary outcome are missing, multiple imputation of 20 data sets will be conducted using an imputation model including all socio-demographic and health related factors assessed at baseline, 4-, 8- and 12-month follow-up. The Markov Chain Monte Carlo (MCMC) method of the SAS procedure PROC MI will be used for multiple imputation and the SAS procedure PROC MIANALYZE will be used for the analysis, considering the variation between the 20 data sets. In sensitivity analysis, the primary outcome will be imputed for all randomized patients, including subjects with no follow-up data. A per-protocol analysis will be done additionally as a sensitivity analysis excluding all patients with non-adherent study physicians (FORTA score at rehabilitation clinic discharge > 2 points or no 2^nd^ study visit with discussion of medication changes performed before rehabilitation clinic discharge) and non-adherent patients (FORTA score of actually used mediation at 8-month follow-up worse by more than 2 points than the FORTA score of medication at rehabilitation clinic discharge) from the intervention group. In a further sensitivity analysis, subjects who received chemotherapy or radiotherapy or had a tumor surgery in the month prior to the 8-month follow-up questionnaire date will be excluded because this may have a very large impact on their QoL, which could superpose all potential effects of the intervention.

As normal distribution can be assumed for the outcome “change in GHS/QoL score”, the primary test statistic will be the two-sample Satterthwaite’s t-test for the mean difference with unequal variances.

All normally distributed secondary endpoints with a continuous scale will also be analyzed with the two-sample Satterthwaite’s t-test. If normal distribution cannot be assumed, the Wilcoxon rank-sum test will be used. All dichotomous secondary endpoints will be tested with a Chi² test. In addition, a generalized estimating equation model will be applied for all outcomes that will be repeatedly assessed during 12 months of follow-up.

A priori defined subgroup analyses will be conducted for groups defined by rehabilitation clinic, age (65–79 / ≥ 80 years), sex, cancer stage (I or II / III or IV), tumor site (lung, breast, prostate, colorectal, or other), baseline EORTC-QLQ-C30 GHS/QoL score (≤ 52 / > 52 points), baseline drug burden (5–9 / ≥ 10 medications), baseline frailty (robust / pre-frail / frail), and use of anti-depressant or anti-psychotic medication at baseline (yes/no).

Because of the multiplicity of tests for subgroup and secondary outcome analyses, all results except for the primary endpoint, will be regarded as exploratory and not confirmatory.

No interim analyses are planned.

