#### Randomization, blinding, and medication review by pharmacist (week 2 of rehabilitation)

The pharmacist in the coordinating center will check correct inclusion into the study and randomize the study participants 1:1 to the intervention and control group. Computer-generated randomization lists will be prepared by the pharmacist before study initiation with randomizer.at, which will be stratified by recruiting center using permuted blocks of random sizes. The block sizes will not be disclosed, to ensure concealment. The allocation sequence will be stored in a locker whose keys will only be available for the pharmacist and his/her deputy. The randomization numbers will be linked to the study participant’s IDs. The study participant’s IDs are used to label the informed consent forms, questionnaires, and all other study materials for a specific patient. The study materials will be packed for each study participant’s ID in the coordinating center and shipped to the rehabilitation clinics. Study participants will get their ID with the package containing the study materials after giving their written informed consent to participate in the study. Staff in the recruiting study centers and the study participants will not see the randomization lists or any randomization number at any time. Unblinding of study participants will be prohibited until end of study month 13 (end of time for collection of 12-month follow-up questionnaires).

The pharmacist in the coordinating center will further perform the medication review with the 4^th^ version of the FORTA list updated in 2021 [7]. Medical diagnoses and drug use obtained from two sources (patient’s medical files and patient’s questionnaires) will be combined to ensure a high completeness.

The use of the FORTA list will be done in two steps:

1st step: Each of the medical diagnoses will need to be checked. The FORTA list comprises the 30 most frequent medical diagnoses and a list of frequently used active substances for each diagnosis. The active substances have a rating from A (indispensable) to D (avoid). The pharmacist will then compare the present medication with the rated active substances in the FORTA list and rates each drug/diagnosis found as follows:

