Appropriate use: The medication is indicated; a drug classified as A (indispensable) or B (beneficial) is prescribed.PIM use: The medication is indicated but a drug classified as C (questionable) or D (avoid) in the FORTA list is given despite available classes A (indispensable) or B (beneficial) alternatives.Underuse: An indication is not treated.

2nd step: Drugs not rated in the first step will then be checked and rated as follows:

Overuse: The medication is prescribed in the absence of an appropriate indication.Appropriate use: The medication is appropriately prescribed according to clinical guidelines for a disease not listed in the FORTA list, which is limited to 30 diseases.

The pharmacist will subsequently calculate the FORTA sub-scores for underuse, overuse, and PIM use for every patient and sum the three scores up to obtain the total FORTA score. Each medication underuse and overuse scores 1 point. Each PIM use scores 2 points.

For patients randomized to the intervention group, the pharmacist will fax an advisory letter to the study physicians stating suggested medication changes to overcome PIM use (by replacing drugs with a C or D rating by drugs with an A or B rating), underuse (by adding drugs with an A or B rating), and overuse (by withdrawal of drugs without indications). If the FORTA list suggests no medication changes, the letter will contain only the sentence: “No medication changes suggested”. For patients randomized to the control group, the letter will include the same sentence: “No medication changes suggested”.

Thus, the study physicians will be partly blinded because they cannot know the randomization group for patients for whom they received the sentence “No medication changes suggested” in the advisory letter from the coordinating center. However, they could still correctly guess that patients with medication changes suggested in the letter are in the intervention group. Thus, due to the nature of the intervention, the study physicians cannot be fully blinded and the study design is only a single-blinded study (only study participants will be blinded).

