#### 2nd study visit for potential medication changes (week 3 of rehabilitation)

The study physician will have a visit with the study participants to discuss his/her medication. This should take place for both the intervention and control group to avoid accidental unblinding of study participants. For study participants in the intervention group, the study physician can follow the advice from the letter of the pharmacist, who conducted the comprehensive medication review with the FORTA list. However, the study physician is free to decide which medication changes he or she will suggest to his/her patient and the patient is also free to decide which changes he/she wants to be implemented.

To maintain blinding of study participants, it is prohibited for the study physician to tell the study participant about the advisory letter he received from the coordinating center or to show the letter to the study participant. Furthermore, it is important for the blinding of study participants that the study physician in addition provides the patient the information that these medication changes could either mean that he/she is part of the intervention group of the study or that these medication changes were based on the physician’s own judgement because the study physicians are allowed to suggest medication changes as part of usual care also to patients randomized to the control group.

In the control group receiving usual care, medication reviews and changes are not prohibited as they are sometimes done as part of usual care in the German oncologic rehabilitation setting. However, medication reviews are usually not comprehensive by checking the total medication with a medication management software and/or PIM lists. To ensure that intervention and control group are treated differently enough to test the intervention, we will not collaborate with study physicians who conduct comprehensive medication reviews with medication management software or apply a PIM list as part of usual care for older cancer patients.

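### The primary analysis is called intention-to-treat but is restricted by two post-randomisation conditions, the intervention visit and any returned questionnaire; the all-randomised analysis is only a sensitivity analysis

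*Protocol article*

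**What the plan says.** All references are to the protocol article.

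- **Label.** Under Statistical methods (H1), the primary endpoint "will be analyzed with an intention-to-treat approach, including all randomized patients in the “Full Analysis Set".
- **Restriction.** The same sentence confines that set to patients "who had a documented visit at the end of rehabilitation and have any follow-up data (4-, 8- or 12-month follow-up".
- **Missing scores inside the set.** "If data for the primary outcome are missing, multiple imputation of 20 data sets will be conducted". A patient who lacks only the 8-month score is therefore kept.
- **All-randomised analysis.** "In sensitivity analysis, the primary outcome will be imputed for all randomized patients, including subjects with no follow-up data". This is the only analysis that covers everyone randomised.
- **Sample size estimation.** The 10% allowance uses nearly the same two conditions: "drop-out defined as no follow-up questionnaire available and/or no documented visit with a study physician at the end of rehabilitation".
- **Order of events.** The section headings read "Randomization, blinding, and medication review by pharmacist (week 2 of rehabilitation" and "2nd study visit for potential medication changes (week 3 of rehabilitation", so the visit follows randomisation.
- **Status of results.** The end of the Statistical methods section makes only the primary endpoint result confirmatory; everything else is exploratory.

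**The concern.** An intention-to-treat comparison is protected because nothing after allocation decides who is counted. Here two later events decide it, and the visit is the harder one to defend.

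- **It is the point of delivery.** The objective is whether an advisory letter to the physician improves quality of life. A letter that leads to no visit is a failure of that strategy. Leaving those patients out answers a narrower question.
- **It can depend on arm.** Patients with a FORTA score of zero are not eligible, so an intervention letter will normally contain suggestions, while every control letter says that none are made. The section on randomisation and blinding concedes of the physicians that "they could still correctly guess that patients with medication changes suggested in the letter are in the intervention group". The person who holds and documents the visit can therefore largely infer the arm, and the visit has less content for a control patient. The Data management section states that study centres will not be monitored.
- **It can discard observed outcomes.** The coordinating center mails the questionnaires itself. A patient without a documented visit may return the 8-month score and still be excluded.

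If the restricted and all-randomised results differ, the plan gives confirmatory status to the restricted one.

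**Working it through.** **1. The plan's own figures.** Inputs from Sample size estimation: difference 5.86; SD of change 16.15 (control) and 27.22 (intervention); two-sided 5%; power 80%; drop-out 10%.

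- A Satterthwaite t-test with the noncentral t distribution needs 231 per arm, 462 in total (power 80.1%).
- 462 / 0.90 = 513.3, rounded up to 514.

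Both agree with the plan. The sample size is not in error.

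**2. How many leave the primary analysis.** 514 − 462 = 52, about 26 per arm if evenly split. The documents do not divide the 10% between the two conditions.

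**3. Bias from the restriction.** In an arm with excluded share q, let D be the mean change in retained patients minus the mean change in excluded patients. Then:

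mean (all) = mean (retained) − q × D

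bias = q_I × D_I − q_C × D_C, which is (q_I − q_C) × D when the gap is the same in both arms.

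Only the overall 10% comes from the documents. The splits and gaps below are assumptions.

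| Excluded, intervention / control | Gap D (points) | Bias (points) | Share of 5.86 |
|---|---|---|---|
| 10% / 10% | any, same in both arms | 0 | 0% |
| 12% / 8% | 10 | 0.04 × 10 = 0.4 | 7% |
| 15% / 5% | 15 | 0.10 × 15 = 1.5 | 26% |
| 10% / 10% | 10 in intervention, 0 in control | 0.10 × 10 = 1.0 | 17% |

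Reversing the arms reverses the sign. The last row shows that equal exclusion rates do not guarantee zero bias if different kinds of patient are lost.

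**4. What such a bias does to the test.** With 231 per arm and the planned SDs, the standard error is √((16.15² + 27.22²) / 231) = 2.08. When there is no true effect, the two-sided 5% error becomes:

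| Bias (points) | Planned SDs | SD 16.15 in both arms |
|---|---|---|
| 0.5 | 5.7% | 6.3% |
| 1.0 | 7.7% | 10.2% |
| 1.5 | 11.1% | 16.9% |

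**5. What it costs to include everyone.** With 257 per arm:

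- If no information were lost to missing data and the effect stayed at 5.86, power would be 84.2%. This is an upper limit.
- If the added 10% had no treatment effect (assumption), the difference would be 0.90 × 5.86 = 5.27. Power would be 76.0% with complete outcomes, or 71.4% if the information stays at 231 per arm.

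**The case against.** **The set is openly defined and the full analysis is prespecified.** True, so an all-randomised result will exist and can be reported. A reader might infer that the trial cannot produce an intention-to-treat result; the documents do not support that. What stands is that the confirmatory test sits on the restricted set under the intention-to-treat label.

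**The plan has safeguards.** The visit is meant to take place in both arms, with scripted cards and a standardised form. Follow-up is mailed to blinded patients with reminders, and by telephone at month 8. Any one of three questionnaires satisfies the follow-up condition. These make strongly unequal loss less likely, but do not exclude it.

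**Patients with no questionnaire have no post-baseline score to analyse.** This stands in part. Every randomised patient should have a baseline score, because its absence is an exclusion criterion, so imputation is possible. A reader might infer that including these patients removes the bias. It does not: imputation borrows from retained patients with similar recorded data and corrects only the part of the gap that those data explain. The gain is clearest for patients excluded solely by the visit condition.

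**The per-protocol visit rule.** A reader might infer that it can exclude nobody, because such patients have already left the primary set. The two rules differ. The Full Analysis Set needs a documented visit; the per-protocol rule needs a visit with discussion of medication changes. The section on the 2nd study visit provides for visits without such discussion, so the rules overlap only in part.

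**Conclusion.** The point holds as a defect of definition. The set that carries the only confirmatory test is labelled intention-to-treat but depends on two post-randomisation events, one of them attendance at the visit where the intervention is given. Up to about 52 of 514 patients are affected on the plan's own allowance.

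The size of any bias is not established. The range of 0.4 to 1.5 points rests entirely on assumed splits and gaps. Its upper end needs a threefold difference in exclusion between the arms and a gap close to one control-group SD (15 against 16.15). A reader might take 1.5 points, or a bias in favour of the intervention, as the expected result; the documents give neither a size nor a direction. Bias is zero if exclusion is unrelated to arm and outcome.

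**What to change.** 1. Delete the visit requirement from the Full Analysis Set.
2. Make the already planned imputed analysis of all randomised patients, as allocated, the primary one. Keep the restricted set as a sensitivity analysis and describe it as a modified set.
3. Name treatment arm in the imputation model. The listed variables are socio-demographic and health-related factors. If arm is omitted, imputing more patients pulls the difference towards zero.
4. State how patients who die before month 8 enter the primary analysis, so that they are not silently removed. Otherwise the set is again conditioned on a post-randomisation event, in older cancer patients of all stages. The planned vital-status follow-up can identify these deaths.
5. Use the visit criterion only in the per-protocol definition.
6. Make the change before any unblinded analysis.

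**Cost.** No new data are needed and both analyses are already planned. The interval will be somewhat wider, and the effect may be diluted to the extent shown in step 5 of the working. That dilution belongs in an intention-to-treat estimate, but the sponsor should decide knowingly whether 514 patients remain enough.

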**Fig. 1 Fig1:**
[figure not shown]
Flow-chart of the OPTIMAL study. Abbreviations: FORTA, Fit fOR The Aged

Recruitment is planned in approximately 10 rehabilitation clinics located all over Germany. The coordinating center is the Division of Clinical Epidemiology and Ageing Research, German Cancer Research Center, Heidelberg, which will not participate in the recruitment of study participants but will conduct follow-ups after the rehabilitation clinic phase of the study.

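### The primary t-test on change fixes the baseline slope at 1 and omits the stratifying clinic, forgoing roughly 10–19% of residual variance: a loss of efficiency, not of validity

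*Protocol article*

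**What the plan says.** Under Statistical methods, the hypotheses concern the change in GHS/QoL from baseline to 8 months, and "the primary test statistic will be the two-sample Satterthwaite’s t-test for the mean difference with unequal variances". No covariate or clinic term is named. The choice carries over to other endpoints: "All normally distributed secondary endpoints with a continuous scale will also be analyzed with the two-sample Satterthwaite’s t-test".

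The randomisation section describes computer-generated lists, "which will be stratified by recruiting center using permuted blocks of random sizes". On the number of centres: "Recruitment is planned in approximately 10 rehabilitation clinics located all over Germany". Missing baseline GHS/QoL is an exclusion criterion, so every correctly included patient has both a baseline score and a clinic.

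Clinic and baseline GHS/QoL (split at 52 points) appear elsewhere in the analysis section only as subgroup factors. A generalized estimating equation model is added for repeatedly measured outcomes, without stated covariates. Everything except the primary endpoint is declared exploratory.

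The sample size section gives the pilot data: the "score increased from baseline (52.41 ± 19.17) to 9-month follow-up (60.96 ± 18.89) by 8.55 (± 16.15) score points".

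**The concern.** Subtracting baseline is the best use of it only if follow-up rises one point for each point of baseline. With a slope below 1, the change score over-corrects: patients who start low tend to gain more, and that predictable part of the change stays in the error term. ANCOVA estimates the slope instead and removes that part.

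Stratified blocks balance the arms within clinics. If clinics differ in mean change, a test without clinic leaves that difference in its error term, and its standard error is larger than the design warrants.

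At stake is the precision of the trial's single confirmatory comparison, which is planned at 80% power with recruitment over 3 years. Both variables are already collected.

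**Working it through.** **Inputs**, all from Sample size estimation: baseline SD 19.17, 9-month SD 18.89, change SD 16.15 (38 MIRANDA patients, used for the control arm); assumed intervention-arm change SD 27.22; target difference 5.86; two-sided 0.05; 231 per arm.

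**1. The plan's own figure.** Welch t-test power from the noncentral t with Satterthwaite degrees of freedom, SDs 16.15 and 27.22:
- SE at 231 per arm = √((260.8 + 740.9)/231) = 2.08.
- Power is 80.1%, so 231 per arm (462 in total) reproduces. 462/0.90 = 513.3, rounded up to 514.

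**2. Baseline slope implied by the pilot SDs.**
- Covariance = (19.17² + 18.89² − 16.15²)/2 = 231.75.
- r = 231.75/(19.17 × 18.89) = 0.640.
- Slope of follow-up on baseline = 231.75/19.17² = 0.631, against the 1 that a change score imposes.

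**3. Residual variance at the control-arm SD.**
- Change score: 16.15² = 260.8.
- Baseline-adjusted: 18.89² × (1 − 0.640²) = 210.7 (SD 14.51).
- Fall: 260.8 − 210.7 = 50.1, and 50.1/260.8 = 19.2%.

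**4. Uncertainty in r.** The Fisher interval with n = 38 runs from 0.40 to 0.80. Holding the baseline and follow-up SDs and letting the change SD follow from r:
- r = 0.40: adjusted 299.0 against change 432.7, a fall of 31%.
- r = 0.80: adjusted 130.4 against change 147.3, a fall of 12%.

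**5. Gain under the plan's unequal SDs.** The document does not say how much of the variance at SD 27.22 baseline explains, so two assumptions bracket it. The planned average variance is (260.8 + 740.9)/2 = 500.9.

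| Assumption | Adjusted variances (control; intervention) | Fall in average variance | Power at 231 per arm |
|---|---|---|---|
| None (planned test) | 260.8; 740.9 | – | 80.1% |
| Same absolute amount (50.1) removed in both arms | 210.7; 690.7 | 10.0% | 84.1% |
| Same fraction (19.2%) removed in both arms | 210.7; 598.4 | 19.2% | 87.8% |

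The last row is a ceiling. It implies slopes of change on baseline of −0.369 in the control arm and −0.438 × 27.22/19.17 = −0.623 in the intervention arm. A model with one common slope (−0.496) adds (0.623 − 0.496)² × 19.17² = 5.9 to each arm's residual variance. The fall is then 18.0% and power 87.3%.

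**6. Clinic.** The document gives no between-clinic variance of the change in GHS/QoL, so no gain from a clinic term can be calculated.

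**The case against.** The strongest defence is coherence. Hypotheses, test and sample size all rest on a t-test on change, the test allows for unequal variances, and the stated numbers reproduce. All of this stands. The pilot correlation is also fragile: it comes from 38 colorectal cancer patients at 9 months, whereas OPTIMAL enrols 22 cancers and measures at 8 months. That stands too and is why a range is given, but a gain appears across the whole interval for r. The GEE model does not fill the gap, because it names no covariates and is exploratory.

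A reader might infer more than the documents support:
- **That baseline is ignored.** It is not; it enters through subtraction with slope 1.
- **That 19% is the share of the available variance reduction that is lost.** Against follow-up alone (variance 356.8), the change score already obtains (356.8 − 260.8)/(356.8 − 210.7) = 66% of what ANCOVA achieves and forgoes 34%. The 19% is the fall in residual variance from change score to ANCOVA.
- **That adjustment is worth 231/0.808 = 286 patients per arm.** The 231 arises only from the assumed SD of 27.22, whereas 0.808 comes only from the SD of 16.15. If the same absolute variance is removed in both arms, the equivalent is 231 × 500.9/450.7 = 257.
- **That chance baseline imbalance is a further harm.** A one-SE imbalance is 19.17 × √(2/231) = 1.78 points, which moves the estimate by 0.369 × 1.78 = 0.66. But 0.66² ≈ 0.43 = 2 × 50.1/231, the excess variance already counted.
- **That omitting clinic is a demonstrated cost.** Stable clinic differences in QoL level cancel in a change score; only differences in mean change remain, and their size is unknown.

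**Conclusion.** The point holds as one of efficiency. The primary test leaves out the stratification factor and uses baseline with a slope that the plan's own data put nearer 0.63 than 1. Baseline adjustment would lower residual variance by about 19% at the control-arm SD, and by about 10–19% on average under the plan's unequal SDs, taking power from 80% to about 84–88%. This assumes that the pilot correlation carries over and that baseline explains intervention-arm variance somewhere between the two cases calculated. Any clinic gain is unquantified.

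It would be wrong to conclude that the planned test is invalid or biased. Under randomisation the change-score estimate is unbiased, and omitting a stratification factor tends to make a test conservative. The change should be made, but the trial does not depend on it.

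**What to change.** Make the primary analysis a linear model (ANCOVA) of 8-month GHS/QoL on arm, baseline GHS/QoL and clinic, with heteroscedasticity-robust standard errors so that the protection against unequal variances is kept. Fit it in each of the 20 imputed data sets and combine the results with PROC MIANALYZE, as already planned. With baseline in the model, the arm coefficient is the same whether the outcome is the 8-month score or the change, so the hypotheses and the 5.86-point target stand. Keep the Satterthwaite t-test as a supportive analysis.

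The sample size can stay as it is, with the gain held as a margin. The cost is protocol and SAP wording, fixed before outcome data are seen, and about 10 of some 460 degrees of freedom. No new data are needed.
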